#### 3.3.4. Nerve Conduction Velocity

Nerve conduction velocity of the tibial and peroneal nerves over the respective nerve compression site are quantified preoperatively and 6 to 12 months postoperatively for both lower extremities using adhesive surface electrodes and a CE-certified neurophysiology device (Viasys Healthcare VikingQuest^®^, Viasys Healthcare GmbH, Höchberg, Germany).

#### 3.3.5. Tissue Biopsies

Intraoperatively harvested tissue biopsies from the tarsal ligament and the fascia of the peroneus longus muscle, are formalin-fixed, stained, and analyzed for histomorphology, cell type distribution, and extracellular matrix composition to assess tissue remodeling. Perineural fat biopsies harvested from entrapment sites are snap frozen and archived into the Collaborative Research Centre (CRC) 1118 diabetes-specific biobank, part of the tissue bank of the National Center for Tumor Diseases (NCT). Collectively, these CRC 1118 biosamples will be analyzed for glucose metabolism pathologies, metabolic pathway regulation, characterization of cellular senescence, inflammation, and fibrosis to decipher the chronic tissue remodeling processes that potentially underlie nerve compression in this cohort.

### 3.4. Participant Timeline

Following initial recruitment, the inclusion and exclusion criteria are applied, and written consent is acquired from each participant. Then, participants undergo a standardized clinical exam and history taking to assess pain intensity, sensory dysfunction, motor function, and to detect neuropathic ulcerations in the skin innervation area of the tibial and/or peroneal nerve in both legs with subsequent electrodiagnostic testing. Nerve decompression surgery is performed, and in-person follow-up exams are scheduled 3 and 12 months post-surgery to repeat the standardized preoperative assessments (Figure 3). Six months post-surgery, a phone interview is conducted to assess pain intensity. Trial participation ends 12 months post-surgery.

### 3.5. Sample Size

Sample size calculation is based on effect sizes achieved in previous clinical studies [40,41,42]. By allocating both lower extremities of one participant as one observation unit, a sample size of *n* = 20 is required for painful and painless participants, respectively, to achieve a power of > 0.8 at a significance level of 5% with an expected drop-out rate of 20%.

### 3.6. Recruitment

Patients potentially suitable for this trial are primarily recruited through diabetic outpatient clinics of the University of Heidelberg, as well as through the peripheral nerve clinic at the BG trauma center, Ludwigshafen, University of Heidelberg.

### 3.7. Allocation and Blinding

The selection of the extremity to be operated on is made after inclusion in the study and completion of the pre-operative tests based on the patient’s preference. A randomized selection of the extremity that undergoes surgery was considered unethical given the often-asymmetrical pain distribution among both legs in our patient population.

Outcomes are assessed through a blinded examiner. The wounds/scars in the operated limb and the corresponding area of the contralateral extremity will be covered by a third person immediately before examination.

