##### Two-Point Discrimination

Two-point discrimination describes the ability to recognize two stimuli as two individual stimuli (and not one stimulus) when they are simultaneously applied in close proximity. Static and dynamic two-point discrimination are assessed in a participant-blinded fashion using a two-point esthesiometer (NCD Medical/Prestige, Los Angeles, CA, USA) according to the protocol of Dellon and Mackinnon [35]. The esthesiometer is placed on the skin with its own weight (10 g), so that the skin is minimally deformed to a standardized extent. The dynamic two-point discrimination assessment follows the same protocol; however, the stimuli are slowly and uniformly moved over the skin in the examination area over a 1.5 cm distance, without applying additional pressure. Two-point discrimination is defined as the minimum distance between two stimuli in millimeter that is correctly recognized as two stimuli in two out of three applications.

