### 3.8. Data Management and Statistics

The collected data will be pseudonymized using case report forms with a unique participant number. Before publication and during statistical analysis the data will be completely anonymized. All collected data are analyzed using descriptive statistics (absolute and relative frequencies or mean, standard deviation, median, interquartile range (IQR), and, if necessary, confidence intervals), and graphic methods to characterize distributions. Because intervention and control group measurements are obtained from one subject and are collected in serial measurements over time, the data are analyzed as matched samples using signed-rank tests to address the following hypotheses.

The targeted surgical release of a mechanically compressed nerve in diabetic, sensorimotor polyneuropathy results in the following:A reduced pain intensity in the innervation area of the nerve distal to the decompression site 3, 6, and 12 months postoperatively, compared to the preoperative pain intensity and compared to an intraindividual non-decompressed control (contralateral lower extremity).A reduced analgesics consumption 3, 6, and 12 months postoperatively, compared to the preoperative baseline.Improved sensation (two-point discrimination, tactile detection threshold) in the innervation area of the nerve distal to the decompression site 3 and 12 months postoperatively compared to the preoperative situation and compared to an intra-individual, non-decompressed control (contralateral lower extremity).Increased isometric muscle strength in target muscles supplied by muscle branches arising from the decompressed nerve distal to the decompression site, 3 and 12 months postoperatively, compared to the preoperative situation and compared to an intra-individual, non-decompressed control (contralateral lower extremity)An increase in nerve conduction velocity across the decompression site 3 and 12 months postoperatively compared to the preoperative situation and compared to an intra-subject non-decompressed control (contralateral lower limb).A lower prevalence of neuropathic ulcerations in the innervated skin area of the nerve distal to the decompression site compared to an intra-individual, non-decompressed control (contralateral lower extremity) in the 12-month postoperative follow-up period.

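### The masking described hides only which leg was operated, so it protects the between-leg comparison but not the before-after tests of sensation and strength

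*Protocol article*

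**What the plan says.** Section 3.7 of the protocol article states "Outcomes are assessed through a blinded examiner". The measure that follows is: "The wounds/scars in the operated limb and the corresponding area of the contralateral extremity will be covered by a third person immediately before examination". The same section fixes when the side is decided: "The selection of the extremity to be operated on is made after inclusion in the study and completion of the pre-operative tests", and the choice rests on the patient's preference.

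Section 3.4 sets the visits: "in-person follow-up exams are scheduled 3 and 12 months post-surgery to repeat the standardized preoperative assessments". Section 3.8 then tests sensation at "3 and 12 months postoperatively compared to the preoperative situation and compared to an intra-individual, non-decompressed control (contralateral lower extremity"). Muscle strength gets the same pair of comparisons, and so does conduction velocity ("An increase in nerve conduction velocity across the decompression site 3 and 12 months postoperatively compared to the preoperative situation", plus the contralateral comparison). The two comparisons stand side by side, with no ranking between them. All are signed-rank tests on matched samples.

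The section on two-point discrimination adds one further masking statement: "Static and dynamic two-point discrimination are assessed in a participant-blinded fashion using a two-point esthesiometer". It concerns the participant, not the examiner.

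**The concern.** The blinding sentence names no limit, and section 3.8 sets out two kinds of comparison that need different protection. A between-leg comparison is protected if the examiner does not know the operated side. A before-after comparison is protected only if the examiner does not know whether a reading is from before or after surgery, and the article describes no step to achieve that.

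Sensory function is part of the primary objective (section 2). The measures concerned depend on how the examiner works: an esthesiometer placed by hand, von Frey hairs, and a handheld dynamometer with the examiner stabilising the limb. A significant before-after gain could therefore be read as blinded evidence of a surgical effect, although the described masking does not support that reading.

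**Working it through.** **1. What the masking conceals in each comparison**

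- *Between legs, at follow-up.* Both legs are covered in matching places, so the side is concealed and the comparison is protected.
- *Before versus after, operated leg.* At baseline the leg has not been chosen and there is no surgical wound to cover. Covering scars at follow-up does not conceal that surgery has taken place. The article does not mention covering the legs at baseline, using separate examiners or withholding earlier values. No protection is described.

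**2. How many tests are exposed**

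The measures are static two-point discrimination, moving two-point discrimination, tactile threshold, toe-flexion strength and toe-extension strength. With one test per measure and visit, 5 measures × 2 visits (3 and 12 months) = 10 before-after tests per cohort. This excludes conduction velocity and does not split the sensory measures by skin area.

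**3. Evaluable pairs**

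Section 3.5 gives 20 participants per cohort and 20% drop-out: 20 × (1 − 0.20) = 16. The sample size itself cannot be reproduced, because the article gives no effect size or SD. The point does not depend on it.

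**4. Effect of a drift b on the before-after test**

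Inputs: n = 16; exact two-sided 5% signed-rank test (section 3.5 does not state sidedness, so two-sided is an assumption); normal paired differences with SD 1; no true surgical effect; drift b added to every difference. The values of b are assumptions. The drift moves the mean by b√16 = 4b standard errors, for example 4 × 0.25 = 1.0 and 4 × 0.5 = 2.0. Simulated rejection rates (100,000 samples; the rate at b = 0 is the test's actual size):

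| Assumed drift b (SD) | False-positive rate, before-after |
|---|---|
| 0 | 4.4% |
| 0.1 | 6.0% |
| 0.2 | 10.1% |
| 0.25 | 13.8% |
| 0.3 | 18.1% |
| 0.5 | 43.0% |

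For scale, 16 pairs have 80% power for a standardised paired effect of about 0.77 (signed-rank, two-sided). The range 0.25 to 0.5 is therefore about one third (0.25/0.77 = 0.32) to two thirds (0.5/0.77 = 0.65) of the effect that the trial could reliably detect.

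**5. The same drift in the between-leg test on changes**

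If the drift is common to both legs, (operated change + b) − (contralateral change + b) = operated change − contralateral change, and b drops out. In the simulation (SD 1 per leg change, legs independent) the rejection rate stayed at 4.3% to 4.6% for every b.

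**The case against.** The strongest reply is that the blinding sentence is not false. It stands under a heading on allocation, after a paragraph on the choice of leg and before a sentence on covering both legs. In that context it can fairly mean blinded to side. A reader might infer that the protocol makes a wrong claim, or that the before-after tests are in fact unblinded. The documents support neither. They are silent on masking of the visit, and a full protocol could provide for it.

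Further objections, and what stands:

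- *Knowledge of the visit is inherent in before-after designs.* Largely true, but that is a reason to limit what the comparison is used for, and this trial already measures a concurrent control leg.
- *Practice from repeat testing is not a blinding fault.* Correct. It would arise under perfect examiner masking, so it is a separate source of drift.
- *Conduction velocity is device-measured.* Correct. A reader might extend the point to it on equal terms, but it is less exposed and is not counted above.
- *The drift sizes are assumed.* Correct. The rates show only what a drift of a given size would do.
- *The contralateral leg is not a clean control.* Correct. A reader might treat its change as a direct measure of examiner and practice drift. It also contains disease course and background treatment. Because the leg is chosen by preference, regression to the mean may differ between legs.

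**Conclusion.** The point holds in a limited form. The described masking conceals the operated side and protects the between-leg comparison. For the before-after tests of two-point discrimination, tactile threshold and muscle strength the article describes no protection, yet section 3.8 gives those tests equal standing.

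The size depends on an unknown drift. At 0.25 to 0.5 SD the false-positive rate per test is about 14% to 43% instead of 4.4%; at 0.1 SD it is 6.0%. The between-leg test on changes stays near 4.4%, provided that the drift is the same in both legs. The figures assume 16 pairs, normal differences and two-sided testing.

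This is neither a contradiction nor a wrong figure, and no change in sample size or significance level follows. It limits which comparison can carry a claim of surgical effect.

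**What to change.** In section 3.7, state that the examiner is blinded to the operated side. Add visit and earlier values only if the examiner is in fact masked to them.

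In section 3.8, for two-point discrimination, tactile threshold and muscle strength:

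- Base the claim of effect on the between-leg difference in change from baseline (operated minus contralateral). Use changes rather than follow-up values, because the legs may differ at baseline when the side is chosen by preference.
- Report the operated leg's before-after change as descriptive, with the contralateral leg's change over the same visits beside it.
- State that the contralateral change reflects drift common to both legs together with disease course and background treatment, and that the between-leg contrast remains open to differential regression to the mean because the leg is not randomised.

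The participant's own knowledge of the operated leg is a separate bias that this change does not remove.

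Cost: wording in two sections. Both legs are already measured at baseline and follow-up, so no new data are needed. The downside is that before-after p-values for these outcomes no longer count on their own as evidence of a surgical effect.

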### 3.8. Data Management and Statistics

The collected data will be pseudonymized using case report forms with a unique participant number. Before publication and during statistical analysis the data will be completely anonymized. All collected data are analyzed using descriptive statistics (absolute and relative frequencies or mean, standard deviation, median, interquartile range (IQR), and, if necessary, confidence intervals), and graphic methods to characterize distributions. Because intervention and control group measurements are obtained from one subject and are collected in serial measurements over time, the data are analyzed as matched samples using signed-rank tests to address the following hypotheses.

The targeted surgical release of a mechanically compressed nerve in diabetic, sensorimotor polyneuropathy results in the following:A reduced pain intensity in the innervation area of the nerve distal to the decompression site 3, 6, and 12 months postoperatively, compared to the preoperative pain intensity and compared to an intraindividual non-decompressed control (contralateral lower extremity).A reduced analgesics consumption 3, 6, and 12 months postoperatively, compared to the preoperative baseline.Improved sensation (two-point discrimination, tactile detection threshold) in the innervation area of the nerve distal to the decompression site 3 and 12 months postoperatively compared to the preoperative situation and compared to an intra-individual, non-decompressed control (contralateral lower extremity).Increased isometric muscle strength in target muscles supplied by muscle branches arising from the decompressed nerve distal to the decompression site, 3 and 12 months postoperatively, compared to the preoperative situation and compared to an intra-individual, non-decompressed control (contralateral lower extremity)An increase in nerve conduction velocity across the decompression site 3 and 12 months postoperatively compared to the preoperative situation and compared to an intra-subject non-decompressed control (contralateral lower limb).A lower prevalence of neuropathic ulcerations in the innervated skin area of the nerve distal to the decompression site compared to an intra-individual, non-decompressed control (contralateral lower extremity) in the 12-month postoperative follow-up period.

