## Abstract

Background: Nerve entrapment has been hypothesized to contribute to the multicausal etiology of axonopathy in sensorimotor diabetic neuropathy. Targeted surgical decompression reduces external strain on the affected nerve and, therefore, may alleviate symptoms, including pain and sensory dysfunction. However, its therapeutic value in this cohort remains unclear. Aim: Quantifying the treatment effect of targeted lower extremity nerve decompression in patients with preexisting painful sensorimotor diabetic neuropathy and nerve entrapment on pain intensity, sensory function, motor function, and neural signal conduction. Study design: This prospective, controlled trial studies 40 patients suffering from bilateral therapy-refractory, painful (*n* = 20, visual analogue scale, VAS ≥ 5) or painless (*n* = 20, VAS = 0) sensorimotor diabetic neuropathy with clinical and/or radiologic signs of focal lower extremity nerve compression who underwent unilateral surgical nerve decompression of the common peroneal and the tibial nerve. Tissue biopsies will be analyzed to explore perineural tissue remodeling in correlation with intraoperatively measured nerve compression pressure. Effect size on symptoms including pain intensity, light touch threshold, static and moving two-point discrimination, target muscle force, and nerve conduction velocity will be quantified 3, 6, and 12 months postoperatively, and compared (1) to the preoperative values and (2) to the contralateral lower extremity that continues non-operative management. Clinical significance: Targeted surgical release may alleviate mechanical strain on entrapped lower extremity nerves and thereby potentially improve pain and sensory dysfunction in a subset of patients suffering from diabetic neuropathy. This trial aims to shed light on these patients that potentially benefit from screening for lower extremity nerve entrapment, as typical symptoms of entrapment might be erroneously attributed to neuropathy only, thereby preventing adequate treatment.

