## 2. Study Objectives

The primary objective of this trial is quantifying the treatment effect size of unilateral surgical release of the tibial nerve in the tarsal tunnel and/or the common peroneal nerve below the muscle fasciae in the proximal lower leg [30] on pain intensity, analgesics consumption, and sensory dysfunction in the skin area supplied by the decompressed nerves.

Secondary objectives are quantifying the treatment effect on target muscle force and fatigability, as well as the incidence of diabetic ulcers in the skin area supplied by the decompressed nerve. Furthermore, tissue biopsies from the perineural fat and overlying compressive fascia are analyzed to explore perineural tissue remodeling in correlation with intraoperatively measured tissue pressures in nerve constriction sites.

Trial registration: German Clinical Trials Register (DRKS); DRKS-ID: DRKS00021151.

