## 3. Materials and Methods

### 3.1. Participants, Eligibility Criteria

A total of 40 type 1 and type 2 diabetic patients (age 18–90 years) suffering from diabetic sensorimotor neuropathy and showing clinical signs of compression of the tibial nerve in the tarsal tunnel and/or the common peroneal nerve below the muscle fasciae in the proximal lower leg on both lower extremities are included in this trial. Of those, *n* = 20 participants suffer from therapy-refractory pain with intensities of 5 and greater on the visual analogue scale (VAS), and another *n* = 20 participants suffer from therapy-refractory hypoesthesia, predominantly localized in the skin areas supplied by the potentially entrapped peripheral nerves.

Detailed eligibility criteria for participating in this trial are as follows:Age 18–90 years;Type 2 or type 1 diabetes mellitus diagnosed according to the guidelines of the German Diabetes Association [31].

And
Diabetic sensorimotor polyneuropathy of both lower extremities [32]:
-Neuropathy Deficit Score > 5 points;-Neuropathy Deficit Score 3–5 points + Neuropathy Symptom Score > 4 points.

And
Clinical evidence of bilateral local nerve compression of the tibial nerve in the tarsal tunnel and/or the common peroneal nerve under the muscle fascia of the peroneus longus muscle:
-Predominant focal (pain) symptoms in the innervation area of the nerve distal to the compression site;-Hoffman–Tinel’s sign over the compression site;-Characteristic electrodiagnostic findings of compression e.g., local conduction block;-Characteristic findings of compression in the MR-neurography, e.g., local T2 weighted hyperintensity of the nerve within the compression site.

And
Bilateral, therapy-refractory pain in the area supplied by the potentially entrapped nerve under conventional, guideline-compliant analgesic therapy (VAS >5);Bilateral hypesthesia in the area supplied by the potentially entrapped nerve defined as a tactile perception threshold greater than 6 g but less than 60 g.Exclusion criteria are as follows:HbA1c in the blood plasma > 8.5% (i.e., poor disease control);Reduced ability to give consent and/or legal capacity (e.g., due to mental illness);Contraindications to lower extremity surgery;Contraindications for electrodiagnostics, such as implanted cardiac pacemaker/defibrillator;Diseases that potentially confound the outcomes of interest, in particular:

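### Analgesics consumption sits in the primary objective, yet it is the only hypothesis compared with baseline alone, and its 6-month test has no matching assessment

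*Protocol article*

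**What the plan says.** Section 2 (Study Objectives) sets the primary objective as the effect of unilateral release "on pain intensity, analgesics consumption, and sensory dysfunction in the skin area supplied by the decompressed nerves". Section 3.8 (Data Management and Statistics) turns this into the hypothesis "A reduced analgesics consumption 3, 6, and 12 months postoperatively, compared to the preoperative baseline", to be examined with signed-rank tests on matched samples. For pain, the same section plans both comparisons: "compared to the preoperative pain intensity and compared to an intraindividual non-decompressed control (contralateral lower extremity".

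In the painful cohort, Section 3.1 requires "Bilateral, therapy-refractory pain in the area supplied by the potentially entrapped nerve under conventional, guideline-compliant analgesic therapy (VAS >5"). Only one leg is operated. The Abstract describes the other as the "contralateral lower extremity that continues non-operative management". Section 3.7 lets the participant choose the leg, after "completion of the pre-operative tests based on the patient’s preference".

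On timing, Section 3.4 (Participant Timeline) says: "Six months post-surgery, a phone interview is conducted to assess pain intensity". The Figure 3 legend gives the 6-month contact the same single purpose.

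**The concern.** The trial's main protection against non-specific change is the within-person comparison of the operated with the non-operated leg. Analgesics consumption does not have that protection. The article gives no unit for it, but it offers no per-leg version and no limb comparison, so it is read here as one quantity per patient.

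Such a quantity can mislead in two directions. Pain in the non-operated leg can keep drug use up even if the operated leg improves. Drug use can also fall for reasons unrelated to surgery: participants are selected for high pain (regression to the mean), they know they were operated, and management changes over a year. Section 4 itself raises placebo as a problem in earlier decompression studies.

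At stake is one of the three domains in the primary objective. A before-after change in it could be published as an effect of surgery, and one of its three planned time points has no assessment behind it.

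**Working it through.** **1. Comparators in Section 3.8, side by side**

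| Hypothesis | Against baseline | Against contralateral leg |
|---|---|---|
| Pain intensity | yes | yes |
| Analgesics consumption | yes | **no** |
| Sensation | yes | yes |
| Muscle strength | yes | yes |
| Nerve conduction velocity | yes | yes |
| Ulceration | no | yes |

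Five of six use the contralateral leg. Analgesics consumption is the only one that rests on baseline alone.

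**2. Role and timing across sections**

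- Section 2: part of the primary objective.
- Section 3.8: tested at 3, 6 and 12 months.
- Section 3.4 and Figure 3 legend: the 6-month contact is for pain intensity only. This conflicts with the 6-month test.
- Section 3.4: the preoperative assessments, which include history taking, are repeated at 3 and 12 months. Drug use may be captured there, although it is not named.
- Section 4: the aim is restated as pain and sensory function, and the secondary outcomes are conduction velocity, motor function and ulceration. Analgesics consumption is in neither list.

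**3. How far the two distortions could go (illustration)**

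From Section 3.5: 20 per cohort and 20% drop-out, so 20 × (1 − 0.20) = 16 evaluable. The article gives no effect size or SD, so the stated sample size cannot be reproduced forward. Solving backwards, 16 pairs give 80% power (two-sided 5%) at a standardised paired effect of 0.77. This uses a noncentral t with effective size 0.955 × 16 = 15.28 to approximate the signed-rank test. Sidedness is assumed, as the article does not state it.

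*Dilution.* Suppose the full effect is 0.77 SD and only a share of it shows in patient-level use because the other leg still hurts:

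| Share showing | Effect (SD) | Power |
|---|---|---|
| 100% | 0.77 | 80% |
| 75% | 0.77 × 0.75 = 0.58 | 56% |
| 50% | 0.77 × 0.50 = 0.39 | 29% |
| 25% | 0.77 × 0.25 = 0.19 | 11% |

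*Drift.* Suppose surgery has no effect but consumption falls for other reasons, in units of the SD of within-person change (16 participants, signed-rank, 10,000 simulated trials):

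| Drift (SD) | Trials declaring a reduction |
|---|---|
| 0 | 2% |
| 0.2 | 10% |
| 0.3 | 18% |
| 0.5 | 44% |
| 0.75 | 77% |

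The shares, the drifts and the 0.77 are assumptions. The tables show direction and sensitivity; they do not forecast this trial.

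**The case against.** The strongest reply is that the authors already treat analgesics consumption as a patient-level, before-after companion to pain. It is patient-relevant, no testing hierarchy in the article rests on it, and a condensed article need not define every measure. Much of that stands, and it rules out several stronger readings.

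- **That Section 2 asks for a drug effect confined to a skin area.** The closing phrase of "pain intensity, analgesics consumption, and sensory dysfunction in the skin area supplied by the decompressed nerves" can attach to sensory dysfunction alone. Section 3.8 gives the analgesics hypothesis no territory, which fits that reading.
- **That analgesic use is recorded at no contact.** Entry requires pain under analgesic therapy, and history taking or the pain history in Figure 3 may capture it at baseline, 3 and 12 months. Absence from the outcome subsections is weak evidence, since ulceration has no subsection there either. Only the 6-month conflict is explicit.
- **That relief of one leg could lower use by at most half.** This assumes equal legs, whereas Section 3.7 says pain is often asymmetrical. If use were proportional to summed pain and the worse leg were operated, scores of 9 and 6 would allow 9/15 = 60%, and 10 and 5 would allow 10/15 = 67%.
- **That the other leg is untreated.** It is non-operated and stays under non-operative management, which may include the drugs being counted.
- **That the pain result cannot be read without drug data.** A systemic drug change acts on both legs, so the limb contrast is largely protected. The before-after pain comparison is the more exposed one.
- **That the painless cohort is tested for reduced use.** Section 3.8 neither says so nor excludes it. With VAS = 0 in the Abstract, the hypothesis has little meaning there.

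The reply leaves two things unanswered: a primary-objective item has no control, and one of its planned tests has no scheduled assessment.

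**Conclusion.** The point holds in a limited form. The plan attributes a fall in analgesics consumption to surgery, but its only comparison cannot separate surgery from drift, regression to the mean or placebo, and persisting pain in the non-operated leg can hide a benefit. The 6-month test contradicts Section 3.4 and the Figure 3 legend, and the outcome's role differs between Sections 2 and 4.

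The conclusion rests on one inference, that consumption is measured per patient. The size of the distortion is unknown. On the assumed inputs, power ranges from 80% down to 11% as dilution grows, and false declarations from 2% up to 77% as drift grows. The limb comparisons for the other hypotheses are not undermined, and no change in sample size follows. It is worth correcting because it affects the primary objective and the remedy is cheap.

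**What to change.** 1. Reconcile Sections 2, 3.4, 3.8, 4 and the Figure 3 legend on the role and timing of analgesics consumption.
2. Move it out of the primary objective and label it a patient-level, uncontrolled supportive outcome.
3. Record it at baseline, 3, 6 and 12 months, using the existing phone call at 6 months.
4. Report change from baseline descriptively in the painful cohort, without attributing it to surgery.

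Do not add an analysis of pain restricted to participants with unchanged analgesics. That selects on a post-treatment variable: those who cut their drugs because surgery helped would be removed, leaving a biased part of at most 20 painful participants.

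The cost is wording, one medication question at each contact that already takes place, and the loss of one nominal primary claim.
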